#### **9.5.3.2 Vital signs**

Blood pressure (systolic and diastolic), pulse rate, and respiratory rate will be measured after at least 5 min rest in supine position. All recordings should be made using the same type of blood pressure recording instrument on the same arm, if possible (on both arms at screening if possible, for inclusion criteria the higher result have to be taken).

Aural body temperature will be determined.

#### **9.5.3.3 ECG recording**

A standard 12-lead ECG will be recorded after at least 5 min rest in supine position using the leads according to Einthoven and Goldberger as well as 6 precordial leads according to Wilson.

|  |  |                           |                       |
|--|--|---------------------------|-----------------------|
|  |  | CRS Study No.:     | 090/18-03.MT   |
|  |  | Sponsor Study No.: | AT1001-035     |
|  |  | EudraCT No.:       | 2018-003684-57 |

Printouts for each ECG (at least three complexes for each standard lead) will include date and time of recording, subject's identification, physician's evaluation, and physician's initials. The date and time of the ECG recordings as well as the overall ECG evaluation and potential abnormal findings of the ECG recordings will be transcribed into the subject's eCRF.

#### **9.5.3.4 Safety laboratory examinations**

Laboratory analyses, except for urinalysis (dipstick), drug screening and alcohol breath test will be carried out by the contract laboratory (Laboratorium Klinische Forschung GmbH, [name]). This laboratory is board-accredited by the "Deutsche Akkreditierungsstelle GmbH (DAkKS)" according to DIN EN ISO 15189 and participates in routine tests for analytical quality.

Urinalysis (dipstick), drug screening and alcohol breath test will be carried out at the study site.

Blood samples for safety laboratory examination will be taken in fasted state.

##### *Clinical chemistry parameters*

Albumin, amylase, P-amylase, bicarbonate, total and direct bilirubin, glucose (fasting), AST, ALT, alkaline phosphatase (AP), lactate dehydrogenase (LDH), creatine phosphokinase (CK), creatinine, urea, uric acid, potassium, sodium, calcium, chloride, total protein, cholesterol (high-density lipoprotein [HDL], low-density lipoprotein [LDL], total), cholinesterase, iron, lipase, magnesium, phosphate, triglycerides

At screening only: FSH and estradiol in females who are post-menopausal < 2 years for confirmation of postmenopausal status (see [Section 7.4](#)).

##### *Hematology parameters*

Hematocrit, hemoglobin, mean corpuscular volume (MCV), mean corpuscular hemoglobin (MCH), mean corpuscular hemoglobin concentration (MCHC), erythrocytes, leukocytes with differential count (neutrophils, lymphocytes, monocytes, eosinophils, basophils), and platelet count.

##### *Serology parameters*

HIV-1/2 antibodies/HIV-1 p24-antigen, HBsAg, and Anti-HCV.

##### *Urinalysis parameters (if able to produce urine)*

Leukocytes, nitrite, pH, protein, glucose, ketone, urobilinogen, bilirubin, blood (dipstick).

Microscopic examination of the sediment will be performed if considered necessary by the investigator.

|  |  |                                                                                             |
|--|--|---------------------------------------------------------------------------------------------|
|  |  | CRS Study No.: 090/18-03.MT
Sponsor Study No.: AT1001-035
EudraCT No.: 2018-003684-57 |
|--|--|---------------------------------------------------------------------------------------------|

*Urine drug screen (if able to produce urine)*

A urine drug screen will be performed using standard urine drug tests (proof of amphetamines, barbiturates, benzodiazepines, cannabinoids, cocaine, methadone, methamphetamine/ecstasy, morphine/opiates, tricyclic antidepressants, phencyclidine).

*Alcohol breath test*

Alcohol testing will be performed using a standard alcohol breath test.

*Pregnancy test in females of childbearing potential*

The serum pregnancy tests will be performed in females of childbearing potential.

### **9.5.3.5 Adverse events**

For definitions, documentation, and rating of AEs refer to [Section 19.4.1](#).

### **9.5.3.6 Pregnancies**

For reporting and documenting pregnancies, refer to [Section 19.5.1](#).

## **9.6 Appropriateness of measurements**

All measurements are carried out according to standard methods.

## **9.7 Statistical methods and determination of sample size**

### **9.7.1 Statistical and analytical plans**

The biometrical evaluation will be carried out by the Department Clinical Data Management of CRS-Mannheim using Statistical Analysis System (SAS) software, Version 9.3 or higher of the SAS System for windows and Phoenix WinNonlin Version 6.4 or higher. Copyright, SAS Institute Inc. SAS and all other SAS Institute Inc. product or service names are registered trademarks or trademarks of SAS Institute Inc., Cary, NC, USA.

#### **9.7.1.1 General statistical considerations - amended**

The following sections describe an overview of the planned statistical methods. A statistical analysis plan (SAP) will be written in which the details of the statistical methods will be described. The SAP will be finalized before database lock. Any deviations from the originally planned statistical analysis or SAP will be described and justified in the clinical study report. Changes known at the time of SAP preparation will also be described in the SAP.

A data review meeting will be held before database hard lock. Protocol deviations will be reviewed during data review meeting. Furthermore, assignment of subjects to the analysis set will be performed.

 Section updated via Amendment 2 to clarify the enrollment of subjects on standard hemodialysis and hemodiafiltration

|  |  |                                                                                             |
|--|--|---------------------------------------------------------------------------------------------|
|  |  | CRS Study No.: 090/18-03.MT
Sponsor Study No.: AT1001-035
EudraCT No.: 2018-003684-57 |
|--|--|---------------------------------------------------------------------------------------------|

Documentation of subjects who did not meet the entry criteria (screening failures) will be collected and filed only in their electronic case report forms (eCRFs); the data will not be listed. The following data will be recorded for screening failures: date of informed consent, demographic data, reason for discontinuation.

Subjects with normal renal function are subjects who fulfill the matching criteria for age, body weight, and gender.

All measured variables and derived PK parameters will be listed individually and, if appropriate, tabulated by descriptive statistics for ESRD subjects on standard hemodialysis, ESRD subjects on hemodiafiltration, subjects with normal renal function matched to ESRD subjects on standard hemodialysis, and subjects with normal renal function matched to ESRD subjects on hemodiafiltration. Figures will be provided as appropriate.

For interference statistical analyses (PK dependent on eGFR) data will be pooled for ESRD subjects and for subjects with normal renal function.

Descriptive statistics will provide the number of observation and the absolute and relative frequency of categorical variables. For the continuous variables, number of observations, arithmetic mean, standard deviation, coefficient of variation (if appropriate), median as well as minimum and maximum will be given.

Descriptive statistics of PK parameters and concentrations will additionally include the geometric mean and the geometric standard deviation. If a zero occurs in a sample, the corresponding geometric mean and geometric standard deviation will be computed, omitting this value.

As appropriate, summaries will be grouped for ESRD subjects on standard hemodialysis, ESRD subjects on hemodiafiltration, subjects with normal renal function matched to ESRD subjects on standard hemodialysis, subjects with normal renal function matched to ESRD subjects on hemodiafiltration, and time of assessment.

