| Dialysate sampling                       |          |       |       |       |       |       |       |       |       |       |       | x              | x     | x     | x     | x     | x  |                    |       |

ESRD = end-stage renal disease, PK = pharmacokinetics

→: sampling to be done continuously, starting from the time point indicated; → | →: end of previous continuous sampling period/start of new continuous sampling period

1: discharge

2: blood draws are to be taken within ± 10 minutes of schedule time until discharge from the study ward and within ± 120 minutes after discharge; the exceptions are the draws at 00:05 past the hour, which must be taken by 00:15 past the hour

3: blood draw to occur immediately before start of dialysis

4: total urine volume MUST be recorded for each collection interval, even if 0 (collection intervals: pre-dose / 0 to 24h, 24 to 48h, 48 to 72h). After discharge on Day 3 subjects will collect the urine at home. The subjects will be instructed to store the urine container in the fridge.

5: the volume of waste dialysate will be recorded at the end of dialysis treatment.

6: just after end of dialysis

|  |  |  |  |  |  |  |  |  |  |  |  |                               |
|--|--|--|--|--|--|--|--|--|--|--|--|-------------------------------|
|  |  |  |  |  |  |  |  |  |  |  |  | CRS Study No.: 090/18-03.MT   |
|  |  |  |  |  |  |  |  |  |  |  |  | Sponsor Study No.: AT1001-035 |
|  |  |  |  |  |  |  |  |  |  |  |  | EudraCT No.: 2018-003684-57   |

Table 2-5: ESRD subjects on hemodialysis - PK sampling time points (period 2)

| Period 2
Study Day                                | 1        |       |                |       |       |       |       |                |       |       |       |       | 2     |       |       |       |       |                    | 3     | 4 |
|------------------------------------------------------|----------|-------|----------------|-------|-------|-------|-------|----------------|-------|-------|-------|-------|-------|-------|-------|-------|-------|--------------------|-------|---|
| hh:mm post dose                                      | Pre-dose | 00:00 | 00:05          | 01:00 | 02:00 | 03:00 | 04:00 | 04:05          | 06:00 | 08:00 | 10:00 | 12:00 | 24:00 | 25:00 | 26:00 | 27:00 | 28:00 | 48:00  | 72:00 |   |

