#### 9.7.1.4 Pharmacokinetics

##### Plasma concentrations

Individual concentrations of migalastat in plasma will be displayed graphically and listed on the original as well as on a logarithmic scale.

For descriptive statistics of plasma migalastat concentrations, values below lower limit of quantification (LLOQ) will be assigned a value of 0. Descriptive statistics of concentrations will be calculated if at least 1/2 of the individual data points have been measured equal or above LLOQ.

Individual data points in the lag-time between time zero and the first quantifiable concentration will be displayed as 0 on the linear concentration scale and they will not be displayed on the logarithmic scale.

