##### Pharmacokinetic characteristics in plasma

Calculation of the PK characteristics will be based on actual blood sampling times [h] (relative to the corresponding administration time) rounded to 2 decimal digits and negative pre-dose times set to zero.

For calculation of the PK parameters the following rules will be applied: At time points in the lag-time between time zero and the first quantifiable concentration, concentrations below LLOQ will be calculated as zero. Concentrations below LLOQ between 2 quantifiable concentrations will be set to missing. Trailing concentrations below LLOQ will set to missing.

Descriptive statistics of PK parameters will be calculated.

For  $t_{\max}$  frequency tables will be drawn based on the nominal time of  $t_{\max}$ .

Figures will be provided.

Individual data points in the lag-time between time zero and the first quantifiable concentration will be displayed as 0 on the linear concentration scale and they will not be displayed on the logarithmic scale.

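### Plasma values below LLOQ become 0 and zeros are then left out of the geometric mean and SD, so these two statistics describe only the quantifiable subjects and the geometric mean is biased upward

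*Protocol*

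**What the plan says.** Four rules in the protocol act together.

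- **Scope.** Section 9.7.1.1: "Descriptive statistics of PK parameters and concentrations will additionally include the geometric mean and the geometric standard deviation". The geometric statistics thus apply to urinary Ae and Fe as well as to concentrations.
- **Zeros.** The next sentence of that section: "If a zero occurs in a sample, the corresponding geometric mean and geometric standard deviation will be computed, omitting this value".
- **Below LLOQ.** Section 9.7.1.4, under plasma concentrations: "For descriptive statistics of plasma migalastat concentrations, values below lower limit of quantification (LLOQ) will be assigned a value of 0". This is stated for plasma only; the urine and dialysate paragraphs give no such rule.
- **When a summary appears.** Same place: "Descriptive statistics of concentrations will be calculated if at least 1/2 of the individual data points have been measured equal or above LLOQ".

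For continuous variables Section 9.7.1.1 also requires "number of observations, arithmetic mean, standard deviation, coefficient of variation (if appropriate), median as well as minimum and maximum will be given", and no omission rule applies to these. Descriptive tables are planned by dialysis method and matched control group, that is, in groups of 3. Pooling is mentioned only for the analysis of PK against eGFR.

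For deriving PK parameters a different rule holds (Section 9.7.1.4, PK characteristics in plasma): "Trailing concentrations below LLOQ will set to missing".

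For urine, the footnotes to the sampling tables in Section 2.2 say "total urine volume MUST be recorded for each collection interval, even if 0". The Synopsis and Section 8 make urine endpoints conditional on the subject being able to produce urine.

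**The concern.** A value below LLOQ is known to be low. Coding it as 0 and then omitting zeros removes it from the geometric mean as if nothing were known about it. The omitted values are always the smallest, so the error has one direction. One table row then describes two sets of subjects: everyone for the arithmetic mean and median, the quantifiable subjects for the geometric mean and SD. Nothing in the protocol requires the second count to be shown.

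The study is essentially descriptive (Section 9.7.1.6) and has three subjects per cell, so the summary tables are the result that readers will use. Migalastat is labelled for dosing every other day (Section 7.2), which makes the 48 h sample in subjects with normal renal function the natural trough value to look at. It is also the sample most likely to be partly below LLOQ. Urinary recovery in ESRD could be distorted in the same way if subjects without urine enter as 0.

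**Working it through.** The protocol states no figure on this point, so there is none to reproduce.

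**1. Where values below LLOQ are plausible.** Inputs: Cmax about 1631 ng/mL (Section 7.4), time to peak about 3 h and half-life about 4 h (Section 7.2). Assuming mono-exponential decay from the peak, C(t) = 1631 × 2^(−(t − 3)/4).

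- 24 h: 1631 × 2^(−5.25) = about 43 ng/mL
- 48 h: 1631 × 2^(−11.25) = about 0.7 ng/mL

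The LLOQ is not in the protocol. On these figures 48 h is the likelier problem, 24 h much less so.

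**2. How many values can be dropped.** At least half must be quantifiable. With n = 3, at least 2 are needed, so at most 1 is omitted. With n = 6, at least 3 are needed, so at most 3 are omitted.

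**3. Inflation of the geometric mean.** Assume log-normal concentrations with σ = √ln(1 + CV²): σ = 0.294 at CV 30% and 0.472 at CV 50%. The CVs are assumptions.

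| Case | Mean of retained standard normal values, m | exp(mσ), CV 30% | exp(mσ), CV 50% |
|---|---|---|---|
| Lowest of 3 omitted | 0.423 | 1.13 | 1.22 |
| Half below LLOQ (LLOQ at the true median) | 0.798 | 1.26 | 1.46 |

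The first row takes any three subjects and drops the lowest. The second fixes the LLOQ at the population median and is the pooled-six case.

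A simulation that applied the half-quantifiable limit, over CVs of 30%, 60% and 100%, gave these ratios to the true geometric mean:

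| Probability below LLOQ | CV 30% | CV 60% | CV 100% |
|---|---|---|---|
| 10% | 1.06 | 1.11 | 1.18 |
| 25% | 1.13 | 1.26 | 1.42 |
| 50% | 1.26 | 1.56 | 1.94 |

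The ratios were the same for n = 3 and n = 6. The limit decides whether a summary is shown; it does not remove the bias.

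**4. Geometric SD.** It rests on the same truncated values, and its error runs the other way. With half below LLOQ the log-scale SD shrinks by √(1 − 2/π) = 0.603. At CV 30% the geometric SD reads exp(0.603 × 0.294) = 1.19 instead of exp(0.294) = 1.34. At CV 50% it reads 1.33 instead of 1.60.

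**5. Worked row.** Plasma values 10, 20 and one below an LLOQ of 5 (illustrative). Geometric mean with omission: √(10 × 20) = 14.1. Arithmetic mean with the zero: 30/3 = 10. On one set of numbers a geometric mean cannot exceed the arithmetic mean; here it does, because the sets differ.

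**6. Urine, if zero volume is scored as Ae = Fe = 0.** The half-quantifiable limit refers to concentrations, so it does not restrain Ae or Fe.

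- Fe of 10%, 5%, 0%: geometric mean √(10 × 5) = 7.1%; mean and median 5%.
- Fe of 10%, 0%, 0%: geometric mean 10%, from one subject; mean 3.3%, median 0%.

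**The case against.** The strongest case on the other side has five parts.

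- **The other statistics keep the zeros.** This stands. A reader might infer that late concentrations and urinary recovery as a whole are averaged only over subjects with drug. The documents do not support that: only the geometric mean and SD are conditional, and the condition is that drug is quantifiable, not that it is present.
- **The primary endpoints are not touched.** This stands. Cmax,0-24, AUC0-t and AUC0-24 would not be zero in a dosed subject and are derived under separate rules.
- **The urine effect is inference.** Largely stands. The rule that sets values to 0 covers plasma only. The protocol records a zero volume but does not say that a subject without urine gets Ae = Fe = 0 rather than not applicable, and recovery among urine producers fits the conditional wording of the endpoint. The point on urine is therefore conditional.
- **The contrast survives.** A reader might infer that inflated control values hide the difference between ESRD and normal function. Taking the half-life of up to 32.3 h in severe impairment (Section 9.2) as a proxy for ESRD before dialysis, the 24 h value is 1631 × 2^(−21/32.3) = about 1039 ng/mL, against about 43 ng/mL: roughly 24-fold. Inflating the control by 46% still leaves about 17-fold. No conclusion turns on this.
- **Some convention is needed, and substitution is biased too.** Partly stands. LLOQ/2 gave 0.88 to 1.38 times the true geometric mean over the simulated settings, against 1.06 to 1.94 for omission. It is better but not clean, so it should not be the main rule. This does not rescue omission, whose error always inflates the geometric mean and is not disclosed in the table.

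**Conclusion.** The concern holds for the geometric mean and geometric SD. At partly below-LLOQ time points the geometric mean is too high, the geometric SD describes a truncated set, and the row is internally inconsistent. In a planned group of 3 with its lowest value omitted, the inflation is about 13% to 22%. In a pooled group of 6 with half the values below LLOQ it is about 26% to 46%; the planned descriptive tables are not pooled in this way. Both ranges rest on log-normal data and assumed CVs of 30% to 50%. How often the situation arises depends on an LLOQ that the protocol does not give; if fewer than half the values are quantifiable, no summary is produced.

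For Ae and Fe the distortion can be larger, but only if zero volume is scored as 0. This is a defect in a stated summary rule, worth correcting because the tables carry the study's results. It does not threaten the main findings.

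**What to change.** Replace the omission sentence in Section 9.7.1.1 with a rule on these lines: if a summary contains a zero or a value below LLOQ, the geometric mean and geometric SD are not calculated; the arithmetic mean, median, minimum and maximum are given with zeros included.

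Two additions go with it:

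- Show the number of zero or below-LLOQ values beside each concentration and urine summary.
- State whether a zero-volume urine interval gives Ae = Fe = 0 or not applicable, and how urine concentrations below LLOQ are handled.

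A geometric mean with LLOQ/2 substituted may be added as a sensitivity display, labelled as such.

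The cost is a change to summary rules and table shells, with no effect on conduct or data collection. The downside is that some late time points lose their geometric mean.

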### 9.7.1.2 Analysis sets

#### Safety Analysis Set

All enrolled subjects who received at least one dose of the study medication will be included in the safety evaluation and the corresponding population.

#### Pharmacokinetic Analysis Set

All subjects for whom the primary PK parameters of migalastat can be derived from at least one treatment period will be included in the PK population.

|  |  |                                                                                             |
|--|--|---------------------------------------------------------------------------------------------|
|  |  | CRS Study No.: 090/18-03.MT
Sponsor Study No.: AT1001-035
EudraCT No.: 2018-003684-57 |
|--|--|---------------------------------------------------------------------------------------------|

### 9.7.1.3 Population characteristics - amended

#### Demographic data

Demographic variables and baseline characteristics will be listed and summarized for ESRD subjects on standard hemodialysis, ESRD subjects on hemodiafiltration, subjects with normal renal function matched to ESRD subjects on standard hemodialysis, subjects with normal renal function matched to ESRD subjects on hemodiafiltration, and overall for the safety and the PK population (provided separately if both populations are different). The descriptive statistics will include number of observations, mean, standard deviation, median, minimum and maximum for continuous variables and number of observations and their percentages for categorical parameters.

#### Consumption history

Data about smoking and alcohol habits, xanthine consumption and drug abuse will be listed and summarized for ESRD subjects on standard hemodialysis, ESRD subjects on hemodiafiltration, subjects with normal renal function matched to ESRD subjects on standard hemodialysis, subjects with normal renal function matched to ESRD subjects on hemodiafiltration, and overall both for the safety and the PK population, if different.

#### Medical and surgical history

Medical and surgical history results will be listed and coded using Medical Dictionary for Regulatory Activities (MedDRA). Coding will be performed with the dictionary version currently used by CRS-Mannheim at time point of study start. The dictionary version will not be changed during the study. Coding terms and investigator terms will be given in the listings.

#### Prior and concomitant medications

Prior and concomitant medications will be listed and coded using the World Health Organization drug dictionary. Coding terms and investigator terms will be given in the listings. Coding will be performed with the dictionary version currently used by CRS-Mannheim at time point of study start. The dictionary version will not be changed during the study.

